## 4.4 Sample size calculation

The trial is powered to detect a difference in the primary end term (cumulative recurrence rate) of 20%. To detect a 20% risk reduction of recurrence between the conditions in a 2 sided test at alpha (=0.05) and a power of 1-beta (=0.80), 107 patients in each condition are necessary. Compensating for loss to follow-up of 10% over the year (107+107/ 0.8=) 238 participants will be recruited.

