**SUMMARY**

***Rationale*:** Major Depressive Disorder (MDD) makes a major contribution to disability and healthcare costs and tends to run a recurrent course. Because the long-term outcome of depression is often unfavourable, there is an urgent need for a (cost-) effective psychotherapy, aimed at the prevention of depression in remitted patients, which is readily accessible at the primary care level. Preventive cognitive therapy (PCT) has already proven to be effective in the prevention of recurrence in group sessions. For both cost-effectiveness and pragmatic reasons, the PARADE study applies PCT in the primary care as a nurse-led self-help. It is hypothesized that adding nurse-led self-help to usual care is clinically superior to care as usual alone for preventing recurrence in recurrent depressive disorder. In addition, it is expected that the intervention dominates the comparator condition in terms of cost-effectiveness.

***Objective***: The primary objective of this study isto evaluate whether nurse-led, cognitive therapy based self-help is (cost-) effective for patients with recurrent MDD in primary care in comparison with usual care. Furthermore this study examines whether nurse-led self-help for patients with recurrent MDD versus usual care alone A) reduces health care utilisation, B) is effective in reducing co-morbid distress, anxiety and somatisation, C) is satisfying according to patients and D) is (cost)-effective in certain subgroups of patients.

***Study design*:** This study is a pragmatic randomised controlled trial among primary care patients with remitted MDD. Patients are randomly assigned to a ‘nurse-led self-help therapy plus usual care’ (134 patients) or ‘usual care alone’ (134 patients). Stratification variables are the number of previous episodes and the type of treatment as usual received during the last episode. It is not possible to blind patients, healthcare providers and main researcher to the intervention in this study due to the nature of the intervention.

***Study population:*** The study population consists of currently remitted patients (age 18-65) with two or more previous episodes of MDD. Participants who have a current mania or a history of bipolar disease, any current organic brain disorder, psychotic disorder or participants with severe sensory disabilities are excluded from participation. Eligible patients are found through a search in the database in the participating primary care practices.

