# 3. STUDY DESIGN

This study is a randomised controlled trial with randomisation at patient level. There will be two parallel groups to evaluate the costs and effects of nurse-led self-help + usual care for 134 primary care patients with remitted MDD versus 134 controls (usual care) at 3, 6, 9 and 12 months follow up. Stratification variables will be the number of previous episodes (cut-off point at 4 or more previous episodes in the last 5 years) and the type of treatment as usual received for the last episode (psychological intervention / AD / no care).

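### Section 4.4 states 10% loss and 238 patients but divides by 0.8, which gives the 268 that the Summary and section 3 randomise; the recruitment target is not fixed

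*Protocol*

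**What the plan says.** Section 4.4 sets the effect twice: "The trial is powered to detect a difference in the primary end term (cumulative recurrence rate) of 20" per cent, and then "To detect a 20% risk reduction of recurrence between the conditions". It gives no control-arm recurrence rate. The error rates are fixed "in a 2 sided test at alpha (=0.05) and a power of 1-beta (=0.80"), and the section concludes that "107 patients in each condition are necessary".

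The allowance for attrition follows: "Compensating for loss to follow-up of 10% over the year (107+107/ 0.8=) 238 participants will be recruited".

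Two other places give the size of the trial. The Summary has: "Patients are randomly assigned to a ‘nurse-led self-help therapy plus usual care’ (134 patients) or ‘usual care alone’ (134 patients"). Section 3 describes the comparison "for 134 primary care patients with remitted MDD versus 134 controls (usual care"). Both come to 134 + 134 = 268. Nothing in the protocol explains why 4.4 has 238.

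**The concern.** One sentence in 4.4 combines a loss rate (10%), a divisor (0.8) and a total (238) that cannot all be true for 214 evaluable patients. The divisor belongs to 20% loss, while the words and the total belong to 10% loss. The total then conflicts with the number to be randomised in two other current sections.

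The number to recruit and the attrition the trial can absorb should each have one value in a protocol. As written, an ethics committee or a practice cannot tell whether recruitment is complete at 238 or at 268. If the lower total were used while losses ran at the rate implied by the divisor, fewer than the required 107 per arm would remain.

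The effect size has a related gap. A 20% difference in a cumulative rate and a 20% risk reduction can mean different things, and sections 7.1.1 and 9.2 express the endpoint as relative risk ratios. Without a control rate, the basis of 107 cannot be confirmed from the text.

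**Working it through.** **Inputs.** From section 4.4: 107 per arm (214 in total), two-sided alpha 0.05, power 0.80, an effect of 20%, loss of 10% in words, divisor 0.8, total 238. From the Summary and section 3: 134 per arm. Control-arm rate: not stated, so a range is used below.

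**Step 1: the recruitment total.** The formula is N = evaluable n / (1 − loss).

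- 10% loss: 214/0.9 = 237.8, so 238, or 119 per arm. This reproduces the total in 4.4.
- Divisor 0.8 (20% loss): 214/0.8 = 267.5, so 268, or 134 per arm. This reproduces the Summary and section 3.
- The printed sum taken literally by operator order: 107 + 107/0.8 = 107 + 133.75 = 240.75. This matches neither total and would inflate only one arm.

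Working backwards, 1 − 214/238 = 10.1% and 1 − 214/268 = 20.1%. So 238 is correct for the stated 10% loss, and the divisor is what does not fit it. The gap is 268 − 238 = 30 patients.

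**Step 2: evaluable patients per arm.**

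| Recruited | Loss | Left per arm |
|---|---|---|
| 238 | 10% | 107.1 |
| 238 | 20% | 95.2 |
| 268 | 10% | 120.6 |
| 268 | 20% | 107.2 |

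Only 238 with 20% loss falls short of 107.

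**Step 3: where 107 could come from.** For two proportions with difference d and mean p̄:

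n = [1.96·√(2p̄(1−p̄)) + 0.842·√(p1(1−p1) + p2(1−p2))]² / d²

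Continuity-corrected: n_c = (n/4)·[1 + √(1 + 4/(n·d))]²

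- Absolute 20 points, 60% v 40% (assumed): n = (1.386 + 0.583)²/0.04 = 96.9; n_c = 106.7, so 107.
- Absolute 20 points at control rates of 57% and 63%: n_c = 106.3, so 107 again. At 50% or 70%, n_c is 103; at 40% or 80%, 91.
- Relative 20% reduction, 83% v 66.4%: n = 106.5, so 107 uncorrected. At 85% v 68%: n = 96.5, n_c = 107.9, so 108.
- Relative 20% reduction at control rates of 50%, 60% and 70%: 388, 270 and 186 per arm uncorrected.

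So 107 fits an absolute 20-point difference at control rates of about 57% to 63% with continuity correction. It fits a relative 20% reduction only at about 83% to 85%.

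**Step 4: power with 95.2 per arm, absolute 20-point difference.** Power = Φ{[d√n − 1.96·√(2p̄(1−p̄))] / √(p1(1−p1) + p2(1−p2))}. For the corrected figure, n is replaced by (n − 1/d)²/n, the inverse of the correction above.

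At 60% v 40%, uncorrected: (0.2 × 9.757 − 1.386)/0.693 = 0.816, so power is 0.79. Corrected: (95.2 − 5)²/95.2 = 85.5; (0.2 × 9.244 − 1.386)/0.693 = 0.667, so power is 0.75.

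| Control rate (assumed) | Uncorrected | Corrected |
|---|---|---|
| 40% or 80% | 86% | 82% |
| 50% or 70% | 81% | 77% |
| 60% | 79% | 75% |

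For comparison, 107 per arm at 60% v 40% gives 84% uncorrected and 80% corrected.

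**The case against.** The strongest reply is that 238 is not a miscalculation. It is the right total for the loss rate that 4.4 states in words, so 0.8 could be a slip for 0.9. On that view section 4.4 needs one digit changed. This is fair as far as it goes, and the point should not be put as 238 being wrong. It does not remove the conflict, because the Summary and section 3 both give the total that the 0.8 divisor produces. A slip confined to the divisor would not explain 134 per arm in two other sections.

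A second reply is that power hardly suffers. That is largely right. The shortfall needs both recruitment of only 238 and loss of 20%. Even then uncorrected power is 79% in the least favourable absolute 20-point case (60% v 40%) and above 80% at control rates of 40%, 50%, 70% and 80%. The figures below 80% elsewhere depend on a continuity correction that the protocol does not mention.

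A reader might also infer that 107 must come from 60% v 40%, or that a relative reduction is ruled out. Neither follows: a band of absolute pairs gives 107, and so does a relative reduction at a high control rate. Section 4.1 does cite 85% recurrence, but over five years, so it cannot be taken as the design rate.

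**Conclusion.** The inconsistency is established from current text alone and needs no assumption. Section 4.4 mixes two versions of the calculation (10% loss, 0.9, 238; and 20% loss, 0.8, 268), and its total contradicts the Summary and section 3 by 30 patients. It should be corrected because the enrolment target is a basic figure of the trial and currently has two values.

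The consequence for power is limited. It arises only if 238 are recruited and 20% are lost. It then amounts to about 95 instead of 107 per arm, with power of about 79% to 86% uncorrected or 75% to 82% corrected. Those ranges assume an absolute 20-point difference and control rates of 40% to 80%, none of which the protocol confirms.

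Two stronger conclusions are tempting but not supported. One is that the trial is underpowered: at 268 with 20% loss, or at 238 with 10% loss, the required 107 per arm is met, and a severe shortfall would need both a relative reading of the effect and a control rate that the protocol does not give. The other is that 268 is the true target: it appears in more places, but 4.4 both states the 10% loss and prints 238, so the documents do not decide it.

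**What to change.** Choose one loss rate, one divisor and one total, and make section 4.4, the Summary and section 3 agree. Either:

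- 10% loss: 214/0.9 = 238, 119 per arm. Change the divisor in 4.4, and change 134 to 119 in the Summary and section 3.
- 20% loss: 214/0.8 = 268, 134 per arm. Change the loss rate and the total in 4.4; the Summary and section 3 stand.

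Put brackets round the sum of the two arms in either case.

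In the same edit, state whether the 20% is an absolute or a relative difference, the control-arm recurrence rate assumed, and the formula used for 107 per arm, including whether it is continuity-corrected. The sponsor has to supply these; the values that happen to reproduce 107 should not be written in as if they were the design assumptions.

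The cost is wording only if the total chosen is the one recruitment already works to. If practices have been working to 238 and 268 is chosen, the cost is 30 more patients.

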# 5. TREATMENT OF SUBJECTS

**5.1 Investigational product/treatment**

## The investigational treatment in this trial is ‘nurse-led self-help’ based on PCT; this preventive cognitive therapy has been demonstrated to be protective in recurrent depression for a period of at least 2 to 5,5 years 42.

## Patients will be offered a detailed treatment manual of the therapy with literature, backgrounds and assignments. This self-help book will enable patients to follow the course of the therapy in their own homes, in their own time. Because experience has shown that patients may come across some difficulties along the course of this therapy, and remitted patients may lack motivation to complete the intervention there will be contact with the nurse on a regular base in order to encourage patients to work through the intervention. The nurses lend (minimal) support and do not engage in a therapeutic relationship with the patients. By implementing the intervention in this way the nurse-led self-help PCT is hypothesized to be (cost-) effective in comparison with usual care, readily accessible at the PCP level and will assume a personalised approach to the patients and their needs.

## Prior to the start of the therapy, a face-to-face meeting with the nurse is planned at the primary care practice (at a maximum of 30 minutes). This meeting involves motivational interviewing, psycho-education on (the course and treatment of) recurrent depression, and an introduction to the nurse-led self-help therapy on the basis of the treatment manual. Apart from this face-to-face meeting there is weekly telephone contact (at a maximum of 15 minutes), initiated by the nurse. During these telephone meetings patients are asked several questions based on a rather strict protocol. These questions comprise: 1) did you fill out Q-IDS-SR questionnaire? 2) did you read and understand the literature belonging to that week? 3) did you make the accompanying **assignments?** and 4) what difficulties did you experience in your assignments? After these 3 questions, patients are shortly prepared for next week’s literature and **exercises**. The contact is of a supportive and facilitating nature and not of a psychotherapeutic nature.

If a nurse notices depressive symptoms during a regular phone-contact or a patient brings up feeling depressed, the nurse emphasizes specific parts of the therapy in order for the patient to cope with these symptoms. Only in the case of a patient expressing suicidal symptoms, the PCP should be notified. These procedures are made explicit in the informed consent papers.

After each contact the nurse summarizes the conversation in a journal on the basis of a checklist. The checklist includes 6 questions:

1) Did the patient fill out the Q-IDS-SR questionnaire of that week?

2) Did the patient read and understand the literature belonging to that week: (yes/no)

- lack of time

- feeling too depressed

- too difficult/did not understand - didn’t feel like

- other …

3) Did the patient make the accompanying assignments: (yes/no)

- lack of time

- feeling too depressed

- too difficult/ did not understand - didn’t feel like

- other …

4) What difficulties did the patient experience? (open)

5) How long did the conversation take (in minutes)

6) What consecutive number is this telephone contact (1 / 2 / 3 / 4 / 5 / 6 / 7 / 8)

This journal is a way to both monitor and promote treatment integrity both on the side of the patient (did he/she read and apply the literature) and the nurse (did he/she go through all the questions). In addition, the contacts with the patients are randomly audiotaped and evaluated during supervision. Any adherence and/or competence issues will be checked this way.

## Nurses will deliver the nurse-led self- help. The face-to-face contacts take place in the primary care practice. The telephone conversations are conducted from the office. The nurses are trained by a professional from [name] group. All practice nurses are experienced in offering cognitive therapy to depressed patients. It takes approximately 1 or 1,5 day to train the nurses. In total, around 15 nurses from 25 different practices will be trained.

## Treatment as usual involves usual care (i.e. standard/routine treatment, including no treatment), as typically provided by the PCP according to the Dutch PCP clinical guidelines (NHG-guidelines). There is no restriction on the use of pharmacotherapy, including the use of anti-depressants during the period form entry to end of follow-up.

Because patients either receive routine care (in the control condition) or an intervention that has been proven to be effective, there is no financial compensation, neither for patients, nor for nurses/PCP’s.

##

## 5.2 Use of co-intervention (if applicable)

*N/A*

## 5.3 Escape medication (if applicable)

*N/A*

# *6.* INVESTIGATIONAL MEDICINAL PRODUCT

*N/A*

# *7.* METHODS

## 7.1 Study parameters/endpoints

### 7.1.1. Main study parameter/endpoint

The primary outcome measure is the cumulative rate of recurrences meeting DSM-IV criteria for a major depressive episode (American Psychiatric Association, 1994) on the SCID 40 at 3, 6, 9, 12 and 15 months in both arms (expressed as relative risk ratios).

Quality of life is measured using the EuroQol 43 and 12-item Short Form Health Survey (SF-12)44. Costs are measured from a societal perspective using the TIC-P45. Costs of the intervention, other health care utilization, patients' out-of-pocket costs and costs due to productivity losses will be included in the economic evaluation. The EuroQol, SF-12 and TiC-P are assessed at 3, 6, 9, 12 and 15 months.

### 7.1.2. Secondary study parameters/endpoints

Secondary outcome is symptom severity as measured weekly during the course of the intervention with the ‘Quick-Inventory of Depressive Symptoms–Self Report’ questionnaire (Q-IDS-SR). At baseline the socio-economic and demographic characteristics are reported (age, gender, education, etc). Also a life-chart (recording a patient’s course of depressive episodes and treatments over the last 5 years) is completed at baseline.

Secondary outcomes will be measured at baseline and at 3,6,9,12 and 15 months follow-up: Q-IDS-SR, Four Dimension Symptom Questionnaire (4-DSQ, comorbid psychopathology), Fatigue Severity Scale (FSS, fatigue), Mac Gill Pain Questionnaire (MPQ, pain), General Self Efficacy Scale (GSES, self-efficacy), Medication Adherence Questionnaire (MAQ, medication adherence) and Nemesis Somatic Illnesses List. At 15 months a Client Satisfaction Questionnaire (CSQ-8) will be assessed in 20 ‘experimental’ patients who responded best, and 20 ‘experimental’ patients who responded worse (in terms of recurrences).

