***Intervention***: The intervention consists of a nurse-led self-help based on Preventive Cognitive Therapy (PCT). Patients are offered a detailed treatment manual of the therapy with literature, backgrounds and assignments, and have weekly telephone contact with a nurse. The therapy consists of eight sessions with a fixed structure. Patients in the control condition receive care as usual.

***Main study parameters/endpoints*:** Primary outcome is the cumulative rate of recurrences of depression meeting DSM-IV criteria, assessed with the Structured Clinical Interview for DSM-IV at baseline and at 3,6,9,12 and 15 months follow-up. For the economic evaluation, quality of life is measured using the EuroQol and 12-item Short Form Health Survey (SF-12). Costs are measured from a societal perspective using the TIC-P. Moderator analyses are conducted for demographic characteristics, number of previous depressive episodes, age of onset of first depression, self-efficacy in preventing depression, satisfaction with PCT, pain and fatigue in order to indentify subgroups that show particularly good response to the intervention.

***Nature and extent of the burden and risks associated with participation, benefit and group relatedness*:** Benefits regarding participation in this trial are the effective preventive cognitive therapy that is offered to patients in a new setting and a regular check for depressive symptoms. Burden associated with participation are the questionnaires that patients must fill in at 3,6,9,12 and 15 months follow-up and the time to complete the assignments of the self-help (approximately 1,5 hours a week). Risks in this trial are very low because usual care, including the use of AD, is permitted in both arms.

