**Secondary Objective(s):**

To study whether nurse-led self-help for patients with recurrent MDD versus usual care alone:

A) reduces health care utilisation

B) is effective in reducing co-morbid distress, anxiety and somatisation

C) is satisfying according to patients

D) is (cost)-effective in certain subgroups of patients, particularly related to (i.e. modified by):

- the number of previous episodes

- type of treatment for the last recurrence (AD, psychological intervention, nothing etc).

- the severity of residual depressive symptoms in the remitted phase

- age of onset of the first depressive episode,

- social economic status (education)

- self-efficacy for managing depression

- symptoms of pain and/or fatigue

- long duration of individual episodes

- socio-demographic factors such as age and gender

- pattern use of antidepressants

The secondary objectives lead to the hypotheses below about effect modification.

*RE: Reduction in health care utilisation*

The substantial economic burden of depression is partly due to an increased health care utilisation. Evidence shows that health care costs of depressed patients are higher compared with matched controls even after adjusting for co-morbidity30. This is not only true for mental but also for general medical care utilization. Therefore, it is hypothesized that by preventing recurrences through this intervention, health care utilisation and related costs in these patients will also be reduced.

*RE: B (cost-) effective in reducing co-morbid levels of psychopathology*

Psychiatric comorbidity in depression is associated with greater symptom severity, severer functional impairments and a more chronic course of the disease. Comorbid psychopathology in depressed patients is common and often involves anxiety and somatisation.

Anxiety consists of irrational and diffuse fears and avoidance behaviour. Somatisation consists of a range of psychosomatic symptoms like headache, muscle pains, cardiovascular and gastrointestinal symptoms31. It is hypothesized that with the reduction of (risk for) recurrences, the co-morbid level of anxiety and/or somatisation will also decrease.

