Unlike anxiety and somatisation, distress is *always* part of the symptomatology of a depressive disorder. Distress contains nonspecific symptoms of psychopathology, ranging from worrying and irritability to fatigue and demoralization. It is hypothesized that symptoms of distress in remitted patients who are in the nurse-led self-help group will decrease due to a lesser likelihood of recurrence.

*RE: C is satisfying according to patients*

Patients’ satisfaction with their treatment is an important predictor of the overall clinical outcome and is a widely used measurement for the evaluation of medical care. In this trial the nurse-led self-help is a new way of delivering a preventive cognitive therapy and satisfaction therefore is unknown. The hypothesis is that patients with higher scores on satisfaction with this format experience a better overall outcome in terms of prevention of recurrences.

*RE: D is (cost-) effective in certain subgroups of patients*

A number of baseline characteristics of the patients that are prognostically relevant for treatment response can be identified. It is hypothesized that patients at higher risk for recurrence benefit the most from this intervention, particularly patients with three to five, or more, prior episodes15;18;19. Besides, patients that already underwent a psychological intervention have the benefit of possible long-term protection for recurrence. Residual depressive symptoms, occurring in many remitted patients, are associated with a much increased risk for recurrence, particularly in the first year 32. Therefore it is hypothesized that with the presence of residual symptoms in remitted patients the risk for recurrence subsequently increases and the intervention will therefore be particularly cost-effective in these patients.

Patients with both fatigue and depression are more disabled and generally have a worse prognosis over time33. Remitted patients with fatigue at baseline are assumed to have an increased risk of developing a new onset of depression34.

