## 7.3 Study procedures

The research assistant checks in- and exclusion criteria. ‘Being remitted’ in this trial is defined as a score of < 10 on the 17-item Hamilton Depression Rating Scale. In order to assess the severity of residual symptoms a baseline, Q-IDS-SR score is calculated. In general, a score of 0-5 represents ‘normal/ no depression’ and a score 6-10 represents ‘mild depression’. A score of 11-15 indicates ‘moderate depression’, 16-20 ‘severe depression’ and 21-27 ‘very severe depression’.

After signing informed consent demographic data and the medical history are collected as part of routine care and in order to enable stratification. After randomisation, the nurse invites intervention subjects into the practice for an initial motivational face-to-face meeting about the course of depression and strategies to prevent recurrence. Also the nurse-led self-help therapy is explained.

Primary outcome is the (repeat) incidence of depressive disorder according to an independent and blinded Structured Clinical Interview for DSM-IV (SCID) 40 at 3, 6 ,9, 12 and 15 months. Secondary outcome is the Four Dimension Symptom Questionnaire (4-DSQ) 31, used every 3 months to assess co-morbid levels of self-reported distress, anxiety symptoms and levels of physical symptoms (somatisation). Satisfaction is measured with the Client/Patient Satisfaction Questionnaire (CSQ-8)46. The CSQ-8 is only assessed at 15 months in 20 ‘experimental’ patients who responded best, and 20 ‘experimental’ patients who responded worse (in terms of recurrences). Satisfaction is best linked to effectiveness this way.

Generic health-related quality of life is measured using both the EuroQol43 and SF-1244. QALYs will be calculated based on the EuroQol using the Dutch tariff by Lamers et al47 . Cost data related to health care uptake will be measured using the TIC-P 45. Medical costs that will be assessed include costs related to the intervention, medication use, hospital admissions, and contacts with healthcare professionals. Unit resource use will be multiplied by their appropriate integral cost prices47. Cost data stemming from absenteeism and presenteeism from paid work will be collected with the PRODISQ. Costs of productivity losses will be estimated using the friction cost method. In a secondary analysis, the human capital will also be used to estimate productivity losses. All questionnaires are assessed at 3, 6, 9, 12 and 15 months.

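### Giving the CSQ-8 only to 20 best and 20 worse responders leaves objective C without a representative satisfaction estimate, and the best 20 cannot be identified

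*Protocol*

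**What the plan says.** Section 2 introduces the secondary objectives with "To study whether nurse-led self-help for patients with recurrent MDD versus usual care alone", and the third of them is "C) is satisfying according to patients". The explanation of that objective, in the same section, gives one hypothesis: "patients with higher scores on satisfaction with this format experience a better overall outcome in terms of prevention of recurrences".

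The only instrument for satisfaction is the CSQ-8. Section 7.1.2 states: "At 15 months a Client Satisfaction Questionnaire (CSQ-8) will be assessed in 20 ‘experimental’ patients who responded best". Section 7.3 repeats the restriction with the word only, and names the other group as "20 ‘experimental’ patients who responded worse (in terms of recurrences"). It then gives the reason: "Satisfaction is best linked to effectiveness this way".

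Three other places bear on this:
- Table 1 lists the CSQ-8 at T5 (15 months) and does not mention a subsample.
- A general sentence in section 7.3 has all questionnaires taken at every follow-up. The specific restriction on the CSQ-8 has to be read as overriding it.
- The Summary lists satisfaction among the moderators: "self-efficacy in preventing depression, satisfaction with PCT, pain and fatigue".

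Section 9 describes no analysis of the CSQ-8. That may sit in a statistical analysis plan and is not held against the protocol here.

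**The concern.** Patients are chosen for the satisfaction measurement on the primary outcome, which is the variable that satisfaction is to be related to. This has three consequences.

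- Objective C asks whether patients find the self-help satisfying. The plain mean of 40 patients, half taken from each end of the outcome, does not estimate the mean of the arm.
- Response is judged by recurrences. Everyone without a recurrence is equally good on that scale, so there is no unique best 20. No rule for choosing is given.
- A correlation computed in the extremes can be larger than the correlation in the arm.

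What is at stake is one stated secondary objective. The sampling is fixed in the protocol and argued for there, and no later analysis plan can recover scores that were never collected.

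**Working it through.** The 20 + 20 has no derivation, precision or power behind it, so there is no figure to reproduce.

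**Inputs.** From the protocol: 134 patients in the intervention arm (section 3), or 238/2 = 119 if the total in section 4.4 holds; 20 + 20 = 40 measured. Assumed: the proportion *p* with any recurrence in the arm. Section 4.4 gives only a 20% difference between arms and neither arm's rate, so *p* is varied from 30% to 60%. The true strength of the satisfaction-recurrence link is also assumed.

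**1. Coverage.** 40/134 = 30%, or 40/119 = 34%. Between 66% and 70% of treated patients have no score.

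**2. Precision of the mean**, as 1.96/√n in SD units:
- n = 40: 1.96/6.32 = 0.31
- n = 134: 1.96/11.58 = 0.17
- n = 107 (the number in section 4.4 before allowance for loss): 1.96/10.34 = 0.19

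**3. Ties at zero recurrences**, as 134 × (1 − *p*):

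| *p* | Tied at zero, of 134 | Of 119 |
|---|---|---|
| 30% | 94 | 83 |
| 40% | 80 | 71 |
| 50% | 67 | 60 |
| 60% | 54 | 48 |

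Twenty would have to be picked from one of these groups. The protocol does not say by whom. Section 7.3 has the questionnaires collected by the main researcher and the research assistant, who are not blinded.

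Ties can also occur at the other end. If counts are Poisson and *p* = 30%, the mean count is −ln(0.70) = 0.357. The share with two or more recurrences is then 1 − 0.70 − 0.70 × 0.357 = 0.050, or about 7 of 134. The rest of the worse 20 would come from patients tied at one recurrence.

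**4. Size of the association and shift of the mean**, by simulation (3,000 replicates per setting, arm of 134, 20 lowest plus 20 highest on the outcome).

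*(a) Ranked by recurrence count.* Poisson counts, ties broken at random, satisfaction falling 0.4 residual SD per recurrence:

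| *p* | r, whole arm | r, 40 selected | Ratio | Mean of the 40 minus arm mean (residual SD) |
|---|---|---|---|---|
| 30% | −0.23 | −0.30 | 1.32 | −0.13 |
| 40% | −0.27 | −0.37 | 1.34 | −0.14 |
| 50% | −0.31 | −0.43 | 1.36 | −0.16 |
| 60% | −0.36 | −0.49 | 1.36 | −0.14 |

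*(b) Ranked on a continuous scale*, such as time to recurrence, with no ties. A true r of 0.20 appears as 0.31, 0.30 as 0.45 and 0.50 as 0.68, a ratio of about 1.4 to 1.6. This is the upper case. It does not describe a selection in which most of the best group tie.

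*(c) Recurrence yes/no, 20 drawn at random from each group*, true difference 0.50 SD. The mean difference is 0.50 SD in both the arm and the 40. The correlation is −0.24 in both at *p* = 40% to 60%, and −0.23 becomes −0.24 at 30%. The unweighted mean still shifts by 0.50 × (*p* − 0.50). At 30% it is 0.10 SD too low, and at 60% it is 0.05 SD too high.

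**5. Test of no association.** With no true link, a t-test of the 20 against the 20 rejects in 5.0% of 10,000 replicates, so its level is kept.

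**The case against.** The strongest reply is that this is deliberate extreme-group sampling for a stated purpose. Section 2 narrows objective C to one hypothesis, that more satisfied patients fare better, and comparing the two ends of the outcome is a recognised way to look for such a link. Step 5 shows that the test is valid. This stands: a reader might infer that objective C cannot be answered at all, and the documents do not support that. The existence and direction of the link remain testable.

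A reader might also infer that the association is inflated whatever is done. It is not. In case (c) inflation is close to nil, and in that case weighting the two groups by their known sizes could recover an arm mean, since every patient has a recurrence assessment. That also stands as a possibility, but the protocol specifies neither a yes/no definition of response nor random draws. Its wording of best and worse reads more naturally as a ranking.

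Three further inferences should be avoided:
- That the protocol plans a 40% recurrence rate in the intervention arm. No rate is given. A 60% v 40% pair does reproduce 107 per arm with a continuity correction, but it is only one assumption that fits.
- That the trial will report a distorted mean or correlation. Section 9 names no CSQ-8 analysis, so what would be reported is unknown.
- That a usual-care comparison of satisfaction was intended and is missing. The phrase about usual care is the shared lead-in to all four objectives, while the explanation of objective C concerns satisfaction with this format, which only the intervention arm receives.

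**Conclusion.** The concern holds in a limited form. As fixed in sections 7.1.2 and 7.3, the CSQ-8 gives objective C no representative estimate of satisfaction. It covers 30% of the arm (34% if the arm is 119), in a mix set by design, with a half-width of about 0.31 SD where the whole arm would give 0.17 SD. The best 20 cannot be identified without a tie rule at any recurrence risk from 30% to 60%.

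Overstatement of the link is conditional on how response is ordered: about 1.3 to 1.4 times for counts, about 1.5 times at a true r of 0.30 under a continuous ordering, and negligible for yes/no with random draws. These ratios rest on assumed effect sizes and recurrence risks. The coverage and half-widths do not, and the tie counts depend only on the assumed risk.

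One secondary objective is affected. The primary outcome, safety reporting and economic evaluation are not.

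**What to change.** - In sections 7.1.2 and 7.3, delete the selection of 20 + 20 and the sentence in 7.3 that justifies it.
- Give the CSQ-8 to all intervention patients at T5, as Table 1 already implies.
- Report the mean score for the whole arm, and relate the score to recurrence in all measured patients. A contrast of extremes remains available as a subset if wanted.
- Word objective C as a description of the intervention arm, so that the shared lead-in does not suggest a comparison with usual care.

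One point is not cured by this. A score taken after the outcome and in one arm cannot act as a treatment moderator, so satisfaction should come off the moderator list in the Summary.

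The cost is eight items for at most 134 − 40 = 94 further patients (119 − 40 = 79 under the smaller total). It falls at an assessment where Table 1 already schedules ten other self-report instruments, and no extra contact is needed.
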